### Study endpoints

#### a) Clinical

Primary: Incidence of clinical episodes of malaria presenting at health facilities defined as a child with an axillary temperature of ≥37.5°C or a history of fever in the past 48 h, together with the presence of *P. falciparum *parasites of any density detected by microscopy and/or RDT in the absence of other detectable cause of fever.

Secondary: (i) mean haemoglobin concentration in children in the two study arms measured in the end of the transmission season survey, (ii) parasite prevalence in children in the two study arms measured at the end of the transmission season.

In addition we will also calculate the incidence of malaria defined by history of fever or temperature of ≥37.5°C and a *P. falciparum *parasitaemia cut-off to give optimum sensitivity and specificity in this setting, and number of children with enlarged spleens at the end of the transmission season.

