### Design

A cluster-randomized controlled study design will be used, as IRS is a community-level intervention and the village cluster as a suitable unit for randomization. All households in all the clusters will be offered LLIN at no cost to the recipients to enable all residents to benefit from this intervention. The clusters will then be randomized into two equal groups; all households in the villages in one group will be offered IRS and those in the other group will not. It is not possible to conduct the IRS in a blinded manner since a placebo would quickly be identified by the community as non-protective. To assess whether DDT IRS and LLINs combined provide better protection against clinical malaria in children than LLINs alone, 75- 125 children aged from 6 months to 13 years old will be sampled according to cluster size enrolled into a study cohort. These children will be followed during the malaria transmission season in 2010 and 2011. Clinical malaria will be recorded by study staff using PCD in close collaboration with government health workers both at the village and health facility levels. Parasites will be detected by a rapid diagnostic test (RDT, Paracheck Pf, Orchid Biomedical Systems, Goa, India) and treatment will follow government treatment guidelines.

The study cohort will be surveyed for malaria indices (parasite prevalence, anaemia and spleen rate) at the end of both transmission seasons to generate data for the secondary endpoints and also at baseline before the year 1 transmission season. Baseline data will be used to compare the 2 groups before the interventions and end of season survey data will be used to attempt to define a *Plasmodium falciparum *parasitaemia cut-off giving optimum sensitivity and specificity for malaria cases in this setting [14].

Exposure to malaria vector mosquitoes and parasites indoors will be assessed using CDC light traps and window traps every 4 weeks from June to December and every 8 weeks from January to May in at least 6 randomly selected households in 16 village clusters in each arm of the study. This will be followed by detection of *Anopheles gambiae *species, parity status and sporozoite infection. A schematic representation of the trial is shown in Figure 1.

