### Clinical data collection and patient treatments

Passive surveillance for malaria will be maintained throughout both transmission seasons. Parents/guardians will be encouraged to take their child to the health centre or health post identified as being closest to their home at any time their child becomes unwell. The Village Health Workers (VHW) who run the health posts will use RDTs in their diagnosis of malaria and treat malaria in children who are enrolled into the study. Nurses placed in strategic health facilities will also perform a RDT in children who present directly to them who are enrolled into the study. Project field workers or nurses will visit each VHW regularly, at least once a week, to record children with malaria episodes.

The parents of any child treated for malaria at a clinical survey or during the passive surveillance will be asked to bring their child to the nearest health facility if the child does not show improvement within 48 h. When such study subjects report to a health facility government nurses will treat the child following Gambian government guidelines and inform the study nurse stationed in that facility. The study nurse will inform the study physician of the case within a minimum of delay. If such study subjects report to the VHW, he/she will advise them to report to the nearest health facility. Referred study subjects will be compensated for transport to the health facilities.

The end of transmission season survey in December 2011 will be the final study visit for all enrolled children and also the final study visit to the villages. The final survey will be similar to the baseline and end of the first transmission season survey in the previous year.

During the course of the study participants are free to receive medication from health personnel outside the study team. During the clinical surveys, iron supplementation will be given to any enrolled child with anaemia (Hb < 9 g/dL). Artemether-lumefantrine (Co-Artem) will be given to any child with a temperature of ≥37.5°C or a history of fever in the past 48 h, and *P. falciparum *parasites detected by RDT in the absence of other detectable cause of fever. The parent/carer of any child we treat for malaria will be asked to bring their child to their nearest health post or facility if the child does not make a recovery within 48 hours. Children with severe malaria will be referred to Basse Health Centre for treatment.

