During the passive surveillance for malaria, parents/carers of study children will be encourage to take their child to the nearest VHW or Health Facility if the child is unwell. In both cases children with symptoms suggestive of malaria will be tested for the presence of parasites using RDTs. Treatment for other conditions will be carried out in accordance with national guidelines and/or referral to Government health facilities.

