### Clinical evaluations

The main morbidity outcome will be incidence of clinical disease assessed by PCD; data from this will provide the primary endpoint of the study. PCD is considered to generate information of more direct relevance to public health than active case detection and is thus more suitable for evaluating population level malaria interventions [16]. Mild malaria and parasitaemia is common in all children in this area of highly seasonal malaria [17,18] and we will enrol children aged 6 months - 13 years. We previously developed a system in Gambian villages where a trained MRC nurse provided diagnostic support to the established VHW in the study villages [19]. Following this experience, in this study the nurses will provide training and ongoing support to the VHW for diagnosis of malaria in consulting study children who report with a history of fever in the last two days using RDT and treatment of malaria. Study nurses at the health facilities will document episodes of malaria in study children who present directly to them on the Case Report Form (CRF). At the health facilities malaria diagnosis will also rely on the use of RDT but, in addition, thick blood films will be made for later staining with Giemsa and microscopy to estimate parasite density in this subset of cases. To facilitate documentation of all clinical events (i.e. clinical consultations by study children), all enrolled children will be issued with enumerated photo identity cards; the study number and village will be recorded for all clinical events on the CRF. The project field workers or nurses that visit each VHW will complete the CRF for all study subjects that consult with the VHW.

All children present in their villages at the surveys will be clinically examined for obvious symptoms and signs of illness, temperature and spleen enlargement. A sample of all the study children, at least 50/village cluster will be randomly selected stratified by age, and these as well as those reporting fever in the last 48 hours and/or with a temperature of ≥37.5°C will be finger pricked for immediate measurement of anaemia and presence of parasites by RDT. Anaemia will be assessed by measuring haemoglobin concentration using a spectrophotometer (HaemoCue^®^) in the field.

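### The formal primary endpoint counts only episodes presenting at health facilities, contradicting the sections that take it from all passive case detection, village health workers included

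*Protocol article*

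**What the plan says.** Study endpoints, a) Clinical, gives the formal definition: "Incidence of clinical episodes of malaria presenting at health facilities", meaning fever or a recent history of it, with parasites at any density found by microscopy, RDT or both.

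The other sections describe a wider set of cases:

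- **Design:** "Clinical malaria will be recorded by study staff using PCD in close collaboration with government health workers both at the village and health facility levels".
- **Clinical data collection and patient treatments:** "The Village Health Workers (VHW) who run the health posts will use RDTs in their diagnosis of malaria", and they also treat enrolled children. Their cases are captured: "Project field workers or nurses will visit each VHW regularly, at least once a week, to record children with malaria episodes".
- **Clinical evaluations:** the main morbidity outcome is assessed by PCD, and the primary endpoint is drawn from those data. The case report form is completed for every study child who consults a VHW.
- **Analytical plan, Outcome 1:** the primary comparison is of incidence measured by PCD, with no restriction to facilities.

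On testing, Clinical evaluations says that facilities also diagnose by RDT but that "in addition, thick blood films will be made for later staining with Giemsa and microscopy to estimate parasite density in this subset of cases". No films are described for children seen by a VHW during PCD.

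**The concern.** The formal definition decides which events enter the primary analysis, and it names only one of the two places where cases are found. An analyst who follows Study endpoints and one who follows the Analytical plan would produce different numerators from the same data. Spraying is not blinded, so this choice should not be left until data exist.

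Each reading has its own problem:

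- **Facility-only:** VHW-diagnosed episodes are lost, and detection depends more heavily on access to a facility. Randomisation itself lists such access among the factors highly correlated with outcome.
- **All PCD:** no events are lost, but the case rule differs by site. A child who is RDT-negative and film-positive can qualify at a facility and cannot at a health post.

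**Working it through.** **1. Can health facility be read to include the VHW health post?** The protocol's own usage says no. For treated children who do not improve: "If such study subjects report to the VHW, he/she will advise them to report to the nearest health facility". Parents are encouraged to "take their child to the nearest VHW or Health Facility if the child is unwell". Facility cases, the ones with films, are called a subset. The two are separate entry points, so the literal definition leaves out the village one.

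**2. Reproduce the plan's figures.** Inputs from Sample Size Rationale, a) Clinical: 110 children per cluster, 22 weeks in each of two seasons, 20% drop-out, rates 0.30 and 0.15 per child-year (used here as control rates), reductions of 30-60%, k from 0.31 to 0.43, 35 clusters per arm. Power and alpha are not stated for this endpoint; 80% and two-sided 5% are assumed.

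Child-years per cluster: 110 × 22/52 × 2 × 0.8 = 74.46 (stated: 74.4).

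With control rate r0, intervention rate r1 and y = 74.4:

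- P = (r0 + r1) / [y (r0 − r1)²]
- K = k² (r0² + r1²) / (r0 − r1)²
- clusters per arm c = 1 + (1.96 + 0.842)² (P + K) = 1 + 7.849 (P + K)

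Smallest case (r0 = 0.30, 60% reduction, k = 0.31): P = 0.174, K = 0.310, c = 4.80, so 5.

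Largest case (r0 = 0.15, 30% reduction, k = 0.43): P = 0.255 / (74.4 × 0.002025) = 1.693, K = 0.1849 × 0.033525 / 0.002025 = 3.061, c = 38.31, so 39.

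Both ends match the stated 5-39. At 90% power the range would be 7-51, so the assumed 80% fits.

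**3. Apply the literal definition.** If a fraction f of PCD cases presents at facilities, both rates are multiplied by f. P becomes P/f and K is unchanged. Power at 35 clusters = Φ(√[34 / (P/f + K)] − 1.96).

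Example, largest case with f = 0.5: P/f + K = 3.385 + 3.061 = 6.446; √(34/6.446) = 2.297; Φ(0.337) = 63%.

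The VHW share is an assumption, shown over 30-70%. For a 30% reduction and k = 0.43:

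| Share lost | Power, r0 = 0.15 | c for 80%, r0 = 0.15 | Power, r0 = 0.30 | c for 80%, r0 = 0.30 |
|---|---|---|---|---|
| 0% | 76% | 38.3 | 84% | 31.7 |
| 30% | 70% | 44.0 | 81% | 34.5 |
| 50% | 63% | 51.6 | 76% | 38.3 |
| 70% | 51% | 69.3 | 67% | 47.2 |

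**4. Elsewhere in the planned range.** With r0 = 0.15, k = 0.43 and half the cases lost, power is 89% for a 40% reduction and 98.5% for 50%. With 70% lost and a 50% reduction, P/f + K = 1.792 + 0.925 = 2.717 and power is 94%. That is the lowest value at any reduction of 50% or more, for either rate and either k.

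These figures hold k fixed. A facility-only count could raise k, because access varies between villages, but the document gives nothing from which to size this.

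**The case against.** The strongest reply is that the intended meaning can be recovered. Clinical evaluations and the Analytical plan both take the primary endpoint from PCD, and VHW consultations go onto the case report form, so one phrase is out of line. This stands. A reader might infer from Study endpoints that the trial plans to discard village cases; the document does not support that, and the finding is a contradiction.

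A reader might also infer that the trial is underpowered against its own plan. The document does not support this either. Sample Size Rationale says only that the 2007 rate of 0.79 was obtained by PCD. If that study counted facility cases alone, the planning rates are already facility rates and power would not fall below plan, although including village cases would still raise it. The tabulated losses also use the smallest planned effect and the largest k, where power is 76% or 84% before anything is lost.

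The power loss and the testing asymmetry cannot both apply: the first belongs to the facility-only reading, the second to the all-PCD reading. On the asymmetry, films are described as measuring density, so they may not have been meant as a second route to a case. The endpoint's wording nevertheless admits them as one.

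Finally, stratifying by presence of a primary health care centre and by location limits imbalance in access between arms. It does not remove variation between villages within an arm.

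**Conclusion.** The contradiction is real and sits in the definition of the primary endpoint. Study endpoints restricts counting to facilities; Clinical evaluations and the Analytical plan do not, and the case-detection procedures run at both levels. It needs correcting because it decides which events count in an open trial.

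The consequence of the literal reading is conditional. It is material for a 30% reduction with k = 0.43, where power falls by 6 to 26 points at a control rate of 0.15 and by 3 to 17 points at 0.30. It is small for reductions of 50% or more. These sizes rest on an assumed 30-70% VHW share, fixed k, and the inferred 80% power and two-sided 5% level.

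**What to change.** Reword the primary endpoint under Study endpoints to count episodes presenting to a village health post (VHW) or a health facility, in line with Clinical evaluations and the Analytical plan.

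Once both sites count, make a positive RDT the test common to both in the primary count, and report film-positive, RDT-negative facility cases as a sensitivity analysis. Tabulating place of presentation by arm is a useful option.

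The cost is wording, since episodes at both levels are already recorded. The RDT rule has a small downside: a few facility cases leave the primary count, and the definition becomes narrower than the one that Clinical evaluations justifies by Gambian research and treatment guidelines. The sensitivity analysis shows what that changes.

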#### b) Entomological

Transmission parameters in the two arms of the study will be estimated from measurements made throughout the transmission season.

Primary: The mean number of female *An. gambiae *s.l./light trap/night inside sleeping rooms.

Secondary: The entomological inoculation rate (EIR) in each study group will be estimated as the mean number of sporozoite infective bites/child/season)

Tertiary: (i) The proportion of mosquitoes exiting houses (since DDT has repellent properties), (ii) the relative abundance of different members of the *An. gambiae *complex in light trap & exit traps collected in each arm of the trial, (iii) the relative abundance of *An. gambiae s.l. *collected outdoors (iv) the parity of *An. gambiae*, to measure mean population longevity.

### Sample Size Rationale

#### a) Clinical

Both LLINs and IRS alone reduce malaria morbidity by approximately 50% [5,6]. The combined impact of these two interventions is unknown. If the effects were simply additive a mean reduction of 75% could be anticipated for the combination, but the effects may be synergistic (e.g. by having a mass killing effect) or antagonistic (e.g. the repellency of DDT reducing *Anopheline *house entry and contact with LLINs). To cover these possibilities we expect that LLINs will reduce incidence by 50%, with LLINs and IRS combined reducing the residual incidence by 30-60% (i.e. 50% vs 65-80% fewer clinical cases of malaria). A study of 3-60 month old children during the end of the rainy season (Sept-Dec) in the URR in 2007 found a seasonal incidence of 0.79 (95% CI: 0.58-1.08) cases/child-years by PCD ([name] pers. comm.); ITN prevalence was 50%. We estimate conservatively that increasing LLIN provision to > 80% and inclusion of older children will reduce incidence rates by about 60-80%, so incidence rates of 0.30 (LLINs) to 0.15 cases/child-years (LLINs & IRS) have been included in the sample size estimations. The study will also record PCD over two high transmission seasons, not 1 as in the [name] study, further enhancing our ability to detect differences between study arms. Estimations for k, the corrected coefficient of variation to adjust for between cluster variation (based on within and between cluster variation) [27], from a cluster trial conducted in the Central River Region of The Gambia in 2006/7 ([name] personal communication) varied from 0.31-0.43 and has been used to explore sample sizes (Figure 2). Two of the 5 districts in URR have 70 villages suitable for the trial with over 100 children aged 6 months-14 years (predicted from the 2003 National Census) and could accommodate an average cluster size of 110 children (range 75-125). We plan to follow these children for 22 weeks covering the peak malaria incidence season each year, which, allowing for a 20% drop out rate over the 2 years, yields 74.4 child-years per cluster. The graphs below indicate a sample size of 5-39 clusters per arm (Figure 2). Since estimates for incidence and drop-out rate are conservative and the value of k may also be reduced by the stratified design, we will recruit 35 clusters in each arm of the trial.

**Figure 2 F2:**
[figure not shown]
**Sample size estimations at varying effect, incidence and coefficient of variation (CV)**.

Data from the same cluster trial quoted above was used to explore sample size considerations for the parasitological and anaemia, endpoints. Considering parasitaemia as a proportion and haemoglobin as a concentration with 35 clusters of 110 children each suggested that sampling half the child cohort would have 80% power to detect a 30% reduction in parasitaemia and a 0.5 mg/mL reduction in haemoglobin at 95% confidence.

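### The haemoglobin power statement is wrong as printed: 0.5 mg/mL is 0.05 g/dL, a difference for which this design would have at most about 34% power at assumed SDs of 1.0-2.0 g/dL, not 80%

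*Protocol article*

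**What the plan says.** The number of clusters is set on malaria incidence: "we will recruit 35 clusters in each arm of the trial". The paragraph after Figure 2 then takes that number as given and uses data from an earlier cluster trial to explore the parasitological and anaemia endpoints. It states that, "with 35 clusters of 110 children each", a sample of half the children "would have 80% power to detect a 30% reduction in parasitaemia and a 0.5 mg/mL reduction in haemoglobin at 95% confidence".

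The Clinical evaluations section sets the number of children to be finger-pricked: "at least 50/village cluster will be randomly selected stratified by age", which is close to half of 110.

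Elsewhere haemoglobin is in grams per decilitre. Under Clinical data collection and patient treatments, "iron supplementation will be given to any enrolled child with anaemia (Hb < 9 g/dL"), and the Discussion also gives its haemoglobin threshold per decilitre. Mean haemoglobin at the end-of-season survey is the first secondary clinical endpoint. The secondary objective is added protection against anaemia, so the expected effect of spraying is higher haemoglobin.

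**The concern.** Read literally, the sentence claims that the survey can pick up a shift of one twentieth of a gram per decilitre in mean haemoglobin. That is a very small difference for a cluster trial with 35 villages per arm, and the unit differs from the one used in the rest of the article.

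This is the only sample-size justification in the article for the first secondary endpoint, and it supports the decision to bleed about half the cohort. A reader who takes it at face value would think the haemoglobin comparison far more sensitive than it is.

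The wording "reduction in haemoglobin at 95% confidence" also runs against the objective, which looks for a gain. That is loose wording; the sign does not alter the power of a two-sided test.

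**Working it through.** **Inputs from the article.** 35 clusters per arm; 110 children per cluster with half sampled, so m = 55 and 35 × 55 = 1,925 per arm; power 80%; 95% confidence, read as two-sided α = 0.05 (sidedness is not stated). Variant: at least 50 per cluster, so 35 × 50 = 1,750 per arm.

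**Inputs not in the article (assumptions).** Haemoglobin SD 1.0-2.0 g/dL; ICC 0-0.20. The k of 0.31-0.43 in the article belongs to the incidence calculation.

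**1. Unit.** 1 g/dL = 10 mg/mL, so 0.5 mg/mL = 0.05 g/dL.

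**2. Can the stated 80% be reproduced?** Not exactly, because the SD and ICC are not shown. The largest SD that would allow it with no clustering is

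SD = 0.05 / [(1.96 + 0.84) × √(2/1,925)] = 0.554 g/dL.

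With 50 children per cluster it is 0.528 g/dL. Any between-village variation lowers these limits.

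**3. Power for 0.05 g/dL.** SE = √[2 × SD² × (1 + 54 × ICC) / 1,925]; power = Φ(0.05/SE − 1.96) + Φ(−0.05/SE − 1.96).

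| SD (g/dL) | ICC 0 | ICC 0.02 | ICC 0.05 |
|---|---|---|---|
| 1.0 | 34% | 19% | 13% |
| 1.5 | 18% | 11% | 8% |
| 2.0 | 12% | 8% | 7% |

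Example: SD 1.0, ICC 0 gives SE = √(2/1,925) = 0.0322, 0.05/0.0322 = 1.55, and power 34%.

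More generous readings do not rescue the figure. At SD 1.0 with no clustering, a one-sided test gives 46%, all 110 children per cluster give 59%, and both together give 71%.

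**4. A check without the child-level SD.** Even with unlimited children per village, 80% power for 0.05 g/dL needs an SD of true village means of at most 0.05 / [2.80 × √(2/35)] = 0.075 g/dL.

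**5. What the design could detect.** The difference detectable with 80% power is 2.80 × SE. For ICC 0-0.10 it runs from 0.09 g/dL (SD 1.0, ICC 0) to 0.46 g/dL (SD 2.0, ICC 0.10), about 2 to 9 times 0.05. At ICC 0.05 it is 0.17-0.35 g/dL.

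**6. Would 0.5 g/dL fit 80%?** Power for 0.5 g/dL, m = 55:

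| SD (g/dL) | ICC 0.05 | ICC 0.10 | ICC 0.12 | ICC 0.20 | ICC 0.23 |
|---|---|---|---|---|---|
| 1.5 | >99.9% | 98% | 97% | 85% | 81% |
| 2.0 | 98% | 87% | 81% | 62% | 56% |

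At SD 1.0 it stays above 99% for every ICC up to 0.20. So 80% is reached near ICC 0.12 at SD 2.0 and near ICC 0.23 at SD 1.5. At lower values power is higher, and at SD 2.0 with a larger ICC it falls below 80%.

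**The case against.** The strongest reply is that this is a slip of the pen: the authors meant 0.5 g/dL, and nothing in the trial depends on it. The 35 clusters per arm rest on malaria incidence, and the haemoglobin sentence only explores a secondary endpoint. What the trial eventually excludes will follow from the estimate and its precision, not from a planned power figure. All of this stands and limits the severity. It does not make the printed figure right, and nothing else in the article corrects it.

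A reader might go further and infer that 80% does not fit 0.5 g/dL either, so that the calculation is wrong under any reading. The article does not support that. The inputs come from an earlier trial that is not shown, and for some of them 0.5 g/dL has close to 80% power. The single 80% also covers two endpoints and may be a shared minimum set by parasitaemia.

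A reader might likewise treat the word reduction as a reversed hypothesis. The objective is clear and the endpoint is a comparison of means, so this is wording only.

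Finally, a journal article may leave the SD and between-cluster variation to the full protocol. Their absence is not the fault here; it only means that the intended figure cannot be recovered from the article.

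**Conclusion.** The statement is wrong as printed. The unit conversion is exact and needs no assumption. That power falls well short of 80% for 0.05 g/dL rests on assumed SDs of 1.0-2.0 g/dL, but it holds over that whole range even with no clustering. With 55 children per cluster and a two-sided test it would fail only at an SD of about 0.55 g/dL or less with essentially no variation between villages.

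A unit slip for 0.5 g/dL is the likely explanation. Whether 80% is then the right power cannot be decided from the article. Severity is moderate to minor: one power statement for a secondary endpoint is affected, while the number of clusters, the primary endpoint and the planned analysis are not.

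**What to change.** Go back to the calculation made from the earlier cluster trial and confirm which difference was used. Restate the sentence in g/dL, with the power confirmed or recomputed for 35 clusters per arm and the 50-55 children per cluster who will be sampled. Describe the effect as a two-sided difference in mean haemoglobin, expected to be higher with spraying. Adding the SD and between-cluster variation used would let readers check the figure, but the correction does not depend on printing them.

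The cost is one corrected sentence and a look at an existing calculation. Recruitment, sampling and analysis do not change.
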